#### Self-reported physical function

Activities of daily living will be assessed using the validated Groningen Activity Restriction Scale [65], which asks participants to rate their level of independence for 18 frequent daily activities, e.g. dressing yourself, going up and down stairs, and making the bed.

#### Height, weight, and body fat

Height will be measured using a portable stadiometer (Seca 213; Seca GmbH, Hamburg, Germany) to the nearest 0.1 cm with participants positioned in the Frankfurt plane. Weight will be measured in minimal clothing and no shoes using electronic weighing scales (Seca 875; Seca GmbH, Hamburg, Germany) to the nearest 0.1 kg. Body fat % and fat mass will be measured using the Bodystat 1500 to the nearest 0.1% and 0.1 kg, respectively.

#### Sitting, standing, and stepping outcomes

Following each data collection session, participants will wear an activPAL4 device on their right thigh for seven full consecutive days to provide a valid and reliable measure of sitting, standing, stepping and breaks in sitting [66, 67]. A nitrile sleeve and medical dressing (Hypafix transparent; BSN Medical Limited, Hull, UK) will be wrapped around the activPAL device to waterproof it before attaching it to their right thigh with a Hypafix dressing. A researcher will assist participants with attaching the device to their thigh and provide them with a copy of the diary during their measurement session. A guidance document and video will also be provided advising participants on how to attach the device in case they need to re-attach it during the monitoring period. Participants will be asked to wear the activPAL continuously during the monitoring period and only remove it if they go swimming to avoid it being lost. Wake and sleep times will be recorded by participants in a diary in addition to any times they undertook paid work or non-wear of the activPAL. Participants will be informed they can contact the research team to discuss any issues while completing this measure. A pre-paid envelope will be provided for participants to post the device back to the research team.

#### Mood, wellbeing, and quality of life outcomes

Sarcopenia-specific quality of life will be measured using the validated SarQoL questionnaire [68], which measures quality of life across seven domains: (1) physical and mental health, (2) locomotion, (3) body composition, (4) functionality, (5) ADL, (6) leisure activities, and (7) fears. The SarQol is scored using an automated code available from www.sarqol.org. Health service use, prescription use and pain relief medication use will be self-reported using a modified version of the Client Service Receipt Inventory [69]. The feasibility of collecting these measures is important to inform a cost-effectiveness evaluation in a full trial. The Positive and Negative Affect Schedule will be used to measure positive and negative mood [70]. Subjective wellbeing will be measured using the Office for National Statistics 4-item scale [71].

#### Process evaluation

A process evaluation, informed by previous research [72, 73], will be conducted throughout the trial to understand factors affecting how the intervention functions, mechanisms explaining its impact and implementation of the trial overall [74]. Questionnaires with scaled, closed and open questions will be completed by intervention participants to explore their experiences with each of the intervention components, barriers and strategies for sitting less, and any other behavioural changes during the study. Control and intervention participants will be asked questions regarding their experiences of completing the study measurements and whether this affected their sitting time or other behaviours. Individuals who withdraw during the study will be invited to complete a questionnaire with closed and open questions to explore the reasons for their withdrawal.

Semi-structured individual interviews will be conducted by video or phone call with a subset of intervention and control participants. Consent to take part in these interviews will be taken at the point of consent for the study. The interviews will explore reasons for taking part in the study in addition to acceptability of the study measurements and if completing these measures led to any changes in behaviour. Interviews with control participants will also explore acceptability of being randomised to this group. For intervention participants, the interviews will evaluate intervention acceptability guided by a theoretical framework for evaluating acceptability of healthcare interventions [75]. It is anticipated that interviews will last for 30–45 min each. Interviews with participants will be conducted until no new data areas are identified and saturation is deemed to have been reached, which is expected to occur with approximately 13 participants from each group [76]. All of the intervention’s health coaches (*n* = 5) will be interviewed to evaluate feasibility and fidelity of the sessions they deliver in the context of the GROW model, using motivational interviewing, assessing capability, opportunity and motivation influences on behaviour, and delivery of the intended BCTs. The number of health coaching sessions that the participants complete will also be recorded. Individuals who were eligible but did not volunteer to take part and those who dropped out during the study will be invited to complete a questionnaire to explore the reasons for this.

#### Participant incentives

Each participant will receive a £10 shopping gift voucher at each data collection time point if they take part in the data collection procedures and return the activity monitor to the research team. Travel expenses will also be reimbursed for visits made to the university for data collection.

### Data analysis

Feasibility analysis will include calculating rates for participant eligibility (number eligible/number assessed for eligibility × 100), recruitment (number randomised/number eligible × 100), retention (number who complete measurements at 3 and 6 months/number enrolled into study × 100), and missing data (number of complete datasets for outcome measures/number of participants enrolled × 100). To assess trial safety, frequency of falls, hospital admissions and adverse events will be calculated for each group in addition to exploring trends in pain and fatigue (using mean ± SD).

All interviews will be transcribed verbatim using the automated transcription feature of Microsoft Teams (Microsoft Corporation, WA, USA) or a transcribing software (Otter.ai; CA, USA) for interviews conducted by other means, e.g. phone call. Transcripts will be subsequently checked for accuracy by the research team. The Framework Method [77] will be used to analyse this data. This will include deductive and inductive coding to generate themes related to positive and negative participant experiences in relation to intervention acceptability, the intervention’s active ingredients, appropriateness of data collection procedures and factors affecting implementation of the trial. Quotes will be used to illustrate these themes. Deductive coding will be used to evaluate the intervention in the context of the theoretical framework for acceptability of healthcare interventions [75]. This framework explores acceptability in the context of affective attitude, burden, ethicality, intervention coherence, opportunity costs, perceived effectiveness, and self-efficacy. Inductive coding will allow for data-driven insights and contextual factors to be explored. Intervention fidelity will be explored in terms of participant and health coach adherence and engagement with the intervention in relation to the planned protocol. Rating scales within the process evaluation questionnaires will be descriptively analysed based on means, SD, and frequencies.

The potential efficacy of the intervention for improving the intended primary (sarcopenia) and secondary outcomes (physical function; sarcopenia-specific quality of life; daily and prolonged sitting, breaks in sitting, standing, and stepping; mood, wellbeing and quality of life) in a definitive trial will be analysed using descriptive statistics. This will include mean ± SD as well as median and interquartile range for continuous data. Frequency, counts, and percentages will be used for categorical data.

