## Methods

### Study design

This is a randomised controlled feasibility trial that will be conducted and reported following the Consolidation Standards of Reporting Trials statement for pilot and feasibility trials [31]. The reporting of the study protocol follows the Standard Protocol Items: Recommendations for Interventional Trials statement [32]. After baseline measures, participants will be randomised to the intervention (Frail-LESS) or control (continue with usual healthcare) groups. Measurements will then be repeated 3 months and 6 months after group allocation. This intervention duration and the timing of measurements was deemed appropriate for determining the feasibility of the study and intervention acceptability. A flow diagram providing an overview of the study can be seen in Fig. 1.

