### Sample size

The target sample size is 40 participants (*n* = 20 in each the intervention and control groups), which is in line with sample size recommendations for pilot and feasibility studies [36, 37]. This number of participants is, therefore, sufficient for addressing the primary objectives of the study relating to feasibility, safety, and acceptability. To allow for 30% attrition, the study aims to recruit 60 participants.

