##### Tailored feedback

Each intervention participant will be provided with a personalised feedback sheet based on their sitting, standing and stepping measurements at each time point (i.e. baseline, 3 months and 6 months). This will include a graphical representation and written explanation of their daily sitting, standing, stepping and number of breaks from sitting.

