### Measurements

#### Trial feasibility outcomes

Feasibility outcomes will include participant eligibility, recruitment and retention rates for the trial. Data completion rates for the intended primary outcome in a future trial (sarcopenia) will also be assessed. Acceptability of the intervention to participants, intervention fidelity and adherence will be evaluated during the process evaluation as described below. Intervention safety will be evaluated in terms of pain (using a 100-mm visual analogue scale [58]) and fatigue (using the Fatigue Severity Scale [59]) in addition to frequency of falls, hospital admissions and adverse events at each data collection time point. Adverse events will also be recorded ad-hoc if reported by a participant.

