#### Expected outcomes for a full trial

The below measures will be collected at baseline and again approximately 3 months and 6 months after group allocation. A data collection session will be arranged to take physical measures at Brunel University London or at participants’ homes, depending on preference and participants’ ability to travel. All questionnaire outcomes will be completed online using Qualtrics (Qualtrics, London, UK) or on paper, depending on participant preference. If it is not possible to arrange a data collection session with a participant within 3 weeks of their expected measurement date for any specific time point (e.g. due to them being uncontactable or unavailable), the data will be considered unobtainable. Similarly, this would be the case if a participant misses two scheduled data collection sessions at any given time point.

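### Safety events are summarised only as a frequency per group, so if attrition differs between arms, the arm that loses more participants will look safer

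*Protocol article*

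**What the plan says.** The protocol article collects safety events under Trial feasibility outcomes: pain and fatigue scores, "in addition to frequency of falls, hospital admissions and adverse events at each data collection time point". Adverse events are also recorded ad hoc when a participant reports one. The summary measure is in Data analysis: "To assess trial safety, frequency of falls, hospital admissions and adverse events will be calculated for each group". The sentence before it prints a numerator and a denominator for eligibility, recruitment, retention and missing data; the safety sentence prints none.

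Three other places bear on how long each participant is observed:

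- Sample size: "To allow for 30% attrition, the study aims to recruit 60 participants".
- Expected outcomes for a full trial: data for a time point are regarded as unobtainable if no session can be held near the due date, or if two scheduled sessions are missed.
- Study design: "After baseline measures, participants will be randomised to the intervention (Frail-LESS) or control". Then: "Measurements will then be repeated 3 months and 6 months after group allocation". Under Tailored feedback the measurement occasions are listed as "at each time point (i.e. baseline, 3 months and 6 months", so the first of them precedes allocation.

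Safety is part of the primary aim and one of the main objectives (end of the Introduction). Being deemed acceptable and safe is one of the criteria for progression to a definitive trial.

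**The concern.** Falls, admissions and adverse events can recur, so the expected count in an arm is the event rate multiplied by the time observed. The plan expects some participants to leave, and those who leave contribute less time. A frequency with no denominator treats everyone as equally observed.

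If the two arms lose participants at different rates, the side-by-side frequencies differ even when the true rates are the same, and the difference favours the arm with the greater loss. Unequal loss is conceivable here. Only the intervention arm is asked to take up five coaching sessions, a wearable device and optional peer meetings. The uncontrolled pilot study in frail older adults cited in the Introduction lost 45% of its participants. Neither fact shows that the intervention arm will lose more, but both are reasons not to rely on equal loss.

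What is at stake is the safety reading that informs progression. For an intervention that prompts frail people to stand and move, falls are an obvious event to watch. Too low a count in the intervention arm would err in the reassuring direction.

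**Working it through.** **Plan's own figure.** 40 / (1 − 0.30) = 57.1, rounded up to 58. The stated recruitment target of 60 is within 2 of this, and 60 × 0.70 = 42 completers. The 30% allowance is therefore consistent with the target. The article gives no event rate, no person-time and no attrition by arm.

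**Inputs.** From the article: 60 recruited at 1:1, so 30 per arm; follow-up of 6 months (26 weeks) with a contact at 3 months (13 weeks); 30% overall attrition. Assumed: how the 30% splits between arms, and the share *f* of leavers who go before the 3-month contact (0 to 1). Leavers who go after it contribute 13 weeks; those who go before it contribute none. The true event rate is taken to be the same in both arms.

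**Formula.** Observed person-weeks in an arm with attrition *d*:

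30 × [(1 − d) × 26 + d × (1 − f) × 13]

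With equal true rates, the expected count ratio is the ratio of person-weeks, and the event rate cancels.

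**Example at 40% versus 20%.**

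- f = 0: 30 × (15.6 + 5.2) = 624, against 30 × (20.8 + 2.6) = 702. Ratio 624/702 = 0.89.
- f = 0.5: 546/663 = 0.82.
- f = 1: 30 × 15.6 = 468, against 30 × 20.8 = 624. Ratio 468/624 = 0.75.

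**Range of assumed splits, all averaging 30%.**

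| Attrition, arm A / arm B | Count ratio, f = 0 | Count ratio, f = 1 |
|---|---|---|
| 30% / 30% | 1.00 | 1.00 |
| 35% / 25% | 0.94 | 0.87 |
| 40% / 20% | 0.89 | 0.75 |
| 45% / 15% | 0.84 | 0.65 |
| 50% / 10% | 0.79 | 0.56 |

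With equal attrition, each arm is observed for 663 person-weeks (f = 0) or 546 (f = 1), out of 30 × 26 = 780 in full. Counts are then 15% to 30% below full follow-up, but the ratio is correct.

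**After the fix.** Dividing each arm's events by its own person-weeks gives an expected rate ratio of 1.00 in every row.

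**Baseline events, if they were pooled.** The article does not say that they will be, and it gives no look-back period. As an illustration, take a look-back of L months at the same rate in both arms, followed by 6 months with a true rate ratio of 2. The pooled ratio is (L + 6 × 2) / (L + 6): 15/9 = 1.67 for L = 3, 18/12 = 1.50 for L = 6, and 24/18 = 1.33 for L = 12.

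**The case against.** The strongest reply is that the sentence is incomplete, not wrong. A journal article may leave denominators for descriptive safety tables to the full protocol or analysis plan, which are not shown. That lowers the weight of the point but does not remove it: the article does state the summary measure, and the measure it states does not suit recurrent events under the attrition it expects.

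A frequency may also be meant to include percentages, since the efficacy paragraph of Data analysis lists frequency, counts and percentages together. But a percentage of those enrolled has the same weakness. A percentage of those observed corrects for leavers with no follow-up, but not for those with partial follow-up.

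Random error is large as well. Assuming 1 fall per person-year and 12.75 person-years per arm (663/52), about 13 falls are expected in each arm. Approximate 95% limits around a true ratio of 1 are exp(±1.96 × √(2/12.75)), or 0.46 to 2.17. The distortions above lie inside that range. This stands as a statement of scale. The distortion is nevertheless systematic, and it flatters the arm with more loss.

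A reader might infer more than the documents support:

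- **A formal between-arm safety comparison.** None is planned, and the progression criterion sets no event threshold. The comparison is implied and descriptive. The Trial Steering Committee also monitors safety.
- **Baseline events added to follow-up events.** The text does not say so. Collection by time point would allow them to be kept apart. The text only leaves pooling open.
- **Visit timing biasing the arms.** The 3-week allowance applies to both arms alike, so it gives no reason for a between-arm difference.
- **Misleading event trends.** Trends are planned for pain and fatigue only, not for events.

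The rule on unobtainable data introduces the measures listed after it, whereas the safety items come earlier in the article. Whether it formally governs them is unclear, although they are collected at the same time points.

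**Conclusion.** The point holds in a limited form. The only stated summary of falls, admissions and adverse events is a frequency per group, with nothing to account for different lengths of observation. Any distortion between arms depends on unequal attrition. Under equal true rates, the count ratio is 1.00 with equal loss, 0.87 to 0.94 at 35%/25% and 0.75 to 0.89 at 40%/20%. These splits are assumptions; the article gives only the overall 30%. No decision is shown to turn on a ratio of this size. The point is worth correcting because safety is a main objective that feeds progression and the correction is cheap. It does not threaten the design.

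**What to change.** In Data analysis, replace the part of the safety sentence on events with wording such as:

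*Events with onset after allocation will be reported by group, separately for falls, hospital admissions and adverse events, as (a) the number of events divided by observed person-time from allocation to last contact, with a 95% confidence interval given for description only, and (b) the number and percentage of observed participants with at least one event. Events reported at the baseline session will be tabulated separately as history.*

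Item (b) should not stand alone, because it still depends on length of observation; item (a) carries the correction. Last contact should be defined so that it fits adverse events reported between sessions as well as those collected at sessions.

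The cost is one sentence, with no extra participants or measurements. Follow-up is already timed from allocation. The article does not say that the date of last contact is recorded, so this should be confirmed. The rates will have wide intervals, which fairly reflects a trial of this size. Person-time does not remove bias if people leave because of the events themselves, so the numbers leaving and their reasons should be shown by arm beside the rates. The planned withdrawal questionnaire can supply reasons from those who complete it.

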### Progression criteria to a definitive trial

Progression from this feasibility trial to a definitive full RCT will be based on the following criteria:The required number of participants are recruited in the intended timeframe.At least 70% of the participants complete the study and provide valid primary outcome data (sarcopenia) at all time points.The intervention is deemed to be acceptable and safe to the participants.The intervention is delivered as planned.

In the case that these criteria are not met, factors affecting implementation of the trial will be explored to identify potential issues that can be adapted in preparation for a full trial.

### Data management

Personal data collected in this study will be handled and stored in line with the U.K. Data Protection Act (2018). Electronic data will be stored on computers that are password protected and online using Qualtrics which is a secure password protected platform. Hard copy data will be stored securely at Brunel University London. Only members of the immediate research team will have access to the data. Participants will be assigned a participant ID number when they enrol into the study, which will be used on all data collection sheets and data files to maintain anonymity. Data collected during measurement sessions will be directly entered into Qualtrics. Interview recordings will be stored securely on Microsoft Teams or an encrypted Dictaphone and will be deleted following data analysis. Qualitative data will be managed using NVivo software (QSR International, Doncaster, Australia). All raw quantitative data will be checked for quality using range checks prior to analysis.

### Trial monitoring

A Trial Steering Committee (TSC) comprising of an independent Chair, an independent expert in the study area, public members, the principal investigator, and co-investigators will monitor progress of the project, protocol adherence, substantial protocol amendments, and participant safety. The TSC will also advise the investigators on all aspects of the project.

The TSC will meet every 3 months. A data monitoring committee is not needed due to the feasibility nature of the study.

### Dissemination strategy

The findings will be disseminated to the public via newsletters distributed to the community, a dedicated University webpage, social media, and a virtual public webinar. Dissemination to academic and practitioner audiences will be via publication in scientific journals and presentation at national and international conferences. All data and dissemination materials will be made open access to maximise reach and impact of the findings.

## Discussion

Older adults living with frailty have a significantly increased risk of losing independence, unplanned hospitalisation and nursing home admission [8]. These risks increase markedly in individuals progressing from mild to moderate and severe levels of frailty [8]. Sarcopenia is a key factor in the development and progression of frailty and is adversely associated with muscle mass, physical function, and the ability to carry out activities of daily living in community-dwelling older adults [4, 5]. Observational evidence suggests that higher volumes of sedentary time are associated with increased risk of sarcopenia and impaired physical function [11, 12]. However, there is a paucity of research evaluating the feasibility, safety, and acceptability of sedentary behaviour interventions for improving sarcopenia and independent living in older adults. This study will address this gap in knowledge, specifically in community-dwelling older adults living with frailty. The findings will improve our understanding of the feasibility, safety, and acceptability of remotely delivered interventions in this population group and inform their suitability for supporting older adults with frailty in reducing and breaking up sitting. In turn, findings could have wider implications for health promotion in a range of social distancing and isolation scenarios such as during pandemics and severe weather, economic constraints, travel and access difficulties, and social isolation. If indicated, the findings will inform a definitive RCT to determine the effectiveness and cost-effectiveness of the intervention for improving sarcopenia and independent living in older adults living with frailty, and could inform public health and clinical care guidelines.

